# The effect of dialectical behaviour therapy in autism spectrum patients with suicidality and/ or self-destructive behaviour (DIASS): study protocol for a multicentre randomised controlled trial

**DOI:** 10.1186/s12888-020-02531-1

**Published:** 2020-03-17

**Keywords:** Autism, Suicidality, Self-destructive behaviour, Dialectical behaviour therapy

## Abstract

**Background:**

Many persons with autism spectrum disorder (ASD) are treated in long-term specialised care. In this population, suicidal behaviour troubles patients, families, and specialists in the field because it is difficult to treat. At present, there is no documented effective therapy for suicidal behaviour in ASD (Autism Research 7:507-521, 2014; Crisis 35:301-309, 2014). Dialectical Behaviour Therapy (DBT) is an efficacious treatment programme for chronically suicidal and/or self-harm behaviour in patients with Borderline Personality Disorder (J Psychiatry 166:1365-1374, 2014; Linehan MM. Cognitive behavioural therapy of borderline personality disorder. 1993). This study will evaluate the efficacy of DBT in persons with ASD and suicidal/ self- destructive behaviour in a multicentre randomised controlled clinical trial.

**Method:**

One hundred twenty-eight persons with autism and suicidal and/or self-harming behaviour will be recruited from specialised mental healthcare services and randomised into two conditions: 1) the DBT condition in which the participants have weekly individual cognitive behavioural therapy sessions and a 2.5 h skills training group session twice per week during 6 months, and 2) the treatment as usual condition which consists of weekly individual therapy sessions of 30–45 min with a psychotherapist or social worker. Assessments will take place at baseline, at post-treatment (6 months), and after a follow-up period of 12 months. The mediators will also be assessed at 3 months. The primary outcome is the level of suicidal ideation and behaviour. The secondary outcomes are anxiety and social performance, depression, core symptoms of ASD, quality of life, and cost-utility. Emotion regulation and therapeutic alliance are hypothesised to mediate the effects on the primary outcome.

**Discussion:**

The results from this study will provide an evaluation of the efficacy of DBT treatment in persons with ASD on suicidal and self-harming behaviour. The study is conducted in routine mental health services which enhances the generalisability of the study results to clinical practice.

**Trial registration:**

ISRCTN96632579. Registered 1 May 2019. Retrospectively registered.

## Background

Recent epidemiological data indicate that Autism Spectrum Disorder (ASD) occurs in 98 out of 10.000 individuals in the general population [1]. Suicidal ideation, self-harm, and suicide attempts are relatively prevalent in autism spectrum disorders with a prevalence from 11 to 66% for suicidal ideation, 1 to 35% for suicide attempts [2, 3]. Premature death by suicide is 7 times more often in persons with ASD [4]. ASD with depression has even higher rates with 85% suicidal ideation and 49% suicidal plans and attempts [5, 6]. Kato and colleagues (2013) stated that “individuals with ASD who have attempted suicide (a) had persistent rather than spontaneous stressors, (b) used more lethal means, and (c) were less connected to psychiatric services than the general population” [7]. This suggests that individuals with ASD may actually be more likely to succeed in their first suicide attempt [7].

Persons with ASD are known to have problems with emotion regulation [8, 9]. Disturbances of affective contact are a core feature of autism [9] and are strongly associated with suicidal ideation and attempts [10–12]. Cassidy and colleagues showed that depression is an important risk factor for suicidality and that social isolation is also associated with suicidal behaviour in autism [6]. Furthermore, ASD is characterised with deficits in expression of feelings and thoughts [10] and anxiety is the most prevalent comorbidity [10, 13]. Both are strongly associated with suicidality. There is no evidence-based treatment available to diminish suicidal ideation and behaviour for this population [10, 14].

In Borderline Personality Disorder, Dialectical Behavioural Therapy (DBT) is an empirically validated treatment for chronically suicidal and/or self-destructive behaviour in adolescent and adult patients [15, 16]. DBT focusses on enhancing emotion regulation skills and encompasses individual therapy, skills training in a group, therapist consultation, and occasional telephone consultation [17].

ASD and BPD share many characteristics: Problems with emotion dysregulation [18]; major problems in interpersonal relationships, identity disturbance, impulsivity, recurrent suicidal behaviour, gestures of threats, affective instability due to marked reactivity of mood, chronic feelings of emptiness, inappropriate intense anger or difficulty controlling anger, and transient, stress-related paranoid ideation and the inability to inhibit various urges, impulses, behaviours, or desires" [19]. DBT addresses these issues and teaches self-regulation, change skills, and skills for self-acceptance and the acceptance of others. The strict and repeated behavioural characteristics of DBT, as well as its focus on building emotion regulation skills, will be especially beneficial for the ASD population due to the autistic preference for predictable instructions and rules of conduct.

A documented mediator is the therapeutic alliance defined as the collaborative bond between therapists and patients [20]. The therapeutic relationship in DBT is considered as a dialectical therapeutic alliance in which the therapist can coach the patient in his/her skills to regulate his/her affect and behaviour [21]. This collaborative agreement between the therapist and the client about the goals and tasks of therapy will also support the preferences of ASD patients for predictable instruction and rules of conduct [22]. The development of a strong alliance between therapists and patients is thought to be especially important for effective intervention [23]. Another mediator is emotion regulation. Emotion dysregulation in ASD is associated with restricted and repetitive behaviour; core features of ASD [18]. Problems with emotion regulation can lead to suicidality [9, 12, 24]. The enhancement of emotion regulation in therapy, such as DBT, may mediate the effects of therapy on suicidality. DBT enhances emotion regulation as it teaches participants to observe and label events, thoughts, emotions, and bodily sensations in a non-judgmental, accepting way [21]. This may be helpful in coping with strong emotions and reducing depression, anxiety, and dysfunctional thoughts and acts [25, 26].

Alexithymia is a trait-like characteristic which causes difficulties in describing subjective emotional experiences. Recent research suggests that individuals with ASD also have high levels of alexithymia, with a prevalence of 40–65% reported in adults with ASD [27–29]. This may moderate therapy effects in a negative way.

In summary the central theme of this study is to determine the efficacy of a short term DBT treatment in persons with ASD and suicidal and/or self-harming behaviour and the mechanisms of change and contextual factors.

### Objectives

#### Primary objective

The primary objective of this study is to determine the efficacy of DBT treatment in persons with ASD on suicidal and/or self-harming behaviour.
► *Hypothesis 1*: DBT treatment is effective in decreasing suicidal and/or self-harming behaviour in the persons with ASD as measured by the combined score on Suicidal Ideation Attributes Scale (SIDAS) [30] and Lifetime Parasuicide Count (LPC) [31] in the first 6 months of treatment, compared to treatment as usual (TAU), and that this difference between the groups is sustained at 12 months.

#### Secondary objectives

The secondary objectives are to determine the efficacy of DBT versus TAU on anxiety, social performance, depression, and quality of life. Further, an economic evaluation will determine the cost-utility of DBT treatment.
► *Hypothesis 2*: DBT reduces social anxiety as measured by Social Interaction Anxiety Scale (SIAS) [32].► *Hypothesis 3*: DBT enhances social functioning as measured by Personal and Social Performance Scale (PSP) [33, 34].► *Hypothesis 4*: DBT reduces depression symptoms as measured by Beck Depression Inventory (BDI-II) [35, 36].► *Hypothesis 5*: DBT enhances quality of life as measured by Manchester Short Assessment of Quality of Life (MANSA) [37] and by EuroQol Group (EQ- 5D) [38].► *Hypothesis 6*: DBT changes severity of ASD symptoms as measured by Social Responsiveness Scale (SRS-A) [39].► *Hypothesis 7*: DBT treatment improves healthcare costs and productivity losses as measured by Treatment Inventory of Cost is Patients with Psychiatric disorders (TIC-P short) [40].

### Other secondary objectives

In the current study we will conduct additional research to explore the mechanisms of change related to the treatment outcome variables. It is hypothesised that both emotion regulation and therapeutic alliance mediate the effects of therapy. The level of alexithymia is hypothesised to moderate the effects of therapy.

## Methods/design

### Design

This study is a single-blind multicentre randomised controlled trial with two arms: dialectical behavioural therapy (DBT) versus treatment as usual (TAU). TAU consists of weekly sessions of 30–45 min with a psychotherapist or social worker. The two groups will be compared at baseline, post-treatment (6 months), and at follow-up (12 months). The mediators will also be assessed mid-treatment at 3 months. All analyses will be performed according to the intention-to-treat principle. This trial meets all the requirements of the SPIRIT Protocol Checklist which provides guidance for protocols of clinical trials [41]. Checklist is provided in Additional file 1.

### Recruitment and study procedures

Adult participants (≥18) will be recruited from outpatient units in Dutch mental healthcare centres with specialised departments in the treatment and care for autism spectrum disorder: Parnassia Psychiatric Institute (Den Haag and Rotterdam), Rivierduinen Psychiatric Institute (Leiden), and Lentis Psychiatric Institute (Groningen). All participants had been diagnosed with ASD by experienced clinicians according to national guidelines, prior to inclusion [42]. Written informed consent will be obtained from each participant.

Patients in participating mental health centres with a diagnosis of ASD and suicidality will be informed about the study by their treating specialist (see Fig. 1) and will be asked for permission to be contacted by the researchers. Potential participants will be phoned by a research assistant and provided with further information about the study.

**Fig. 1 Fig1:**
[figure not shown]
Trial flow *diagram*. Assessments will take place at baseline, at post-treatment (6 months), and after a follow-up period of 12 months. The mediators will also be assessed at 3 months

Patients will have 2 weeks to decide about their participation. If the patient is willing to participate, informed consent will be signed. To verify the clinical diagnosis of ASD, we will use a cut-off ≥70 on the 28-item Short version of the AQ-28 [43, 44]. Patients who are willing to participate will be screened for suicidal and/or self-destructive behaviour and level of suicidality/self-harming behaviour in the last year. After screening, baseline data will be collected and participants will be randomly allocated to one of the two study groups. Participants who are randomised to DBT will start with two commitment sessions. After commitment is reached, the goals and targets of treatment will be discussed. A personalised treatment contract will be formulated and signed by the individual therapist and the patient. After 6 months, post-treatment assessment will be performed in both conditions. After 12 months, a follow-up measurement for all primary and secondary outcomes will be performed in both conditions. The mediators will also be assessed mid-treatment at 3 months.

### Inclusion criteria

Age between 18 and 65 yearsMeets DSM-5 criteria for autism spectrum disorder [45]Suicidal ideation (SIDAS score ≥ 21) [30] and/or level of suicidality/self-harming behaviour rated as severe on the LPC (score = 2 on any item) [31]Outpatient status

### Exclusion criteria

IQ < 80 (only assessed with WAIS-IV if baseline testing is difficult because of intellectual deficits)Addiction to illicit drugs and in need of clinical detoxificationInsufficient mastery of the Dutch language

### Randomisation

One block of 16 random assignments will be generated for each participating mental health centre. Each block will have 8 assignments for each condition: DBT or control group, treatment as usual. If a centre includes more patients, new blocks of random assignments will be generated. The blocks and random assignments will be generated using a scientific randomisation programme (www.randomizer.org) by the independent randomisation bureau of Parnassia Psychiatric Institute. Participants will be informed about their allocation by mail. The therapists will be informed about the participation of their client and about which condition the client has been allocated.

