## Discussion

Because there are no empirical data to guide practitioners in the treatment of suicidality in persons with ASD, it is important to determine if DBT is an effective intervention to reduce or prevent suicide ideation and attempts [2, 5, 6]. Given that DBT has been found to effectively decrease parasuicidal behaviour and other areas of behavioural dyscontrol in the treatment of emotion regulation problems in patients with a diversity of disorders [59], we hypothesise that DBT will also be effective in decreasing suicidality for individuals with autism.

This study has several strengths. Foremost, it is the first single-blind randomised controlled clinical trial to examine the efficacy of DBT in people with autism and suicidality. Furthermore, this study is conducted in routine mental health services which enhances the generalisability of the study results to regular clinical practice. Finally, our sample is relatively large and consists of both men and women.

No major difficulties are expected with regard to the recruitment of persons with autism. However, due to the traditional cautiousness of some therapists, recruitment may be hindered as therapists may be more reluctant to recommend this treatment to their clients. Therefore, information sessions for therapist about the study will be held at the participating mental health centers to help facilitate recruitment. Since suicidality is known to be an enduring problem in people with ASD, a main limitation of this study is the short follow-up. It could also be argued that the contact time in the control condition (TAU) will not match that of DBT. However, TAU consists of standard care for persons with ASD and suicidality and the aim of the study is to investigate the efficacy of DBT treatment for persons with ASD and suicidality or self -destructive behaviour. The comparison of DBT treatment and a control condition will provide further information about the efficacy of DBT for this population. If DBT is found to effectively reduce suicidality and self-destructive behaviour in autism patients, new guidelines for the conceptualisation and the use of DBT can be drafted.

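### A fixed, published block of 16 per centre lets anyone tracking every allocation deduce up to about 1.8 assignments per block; undisclosed, varying large blocks would remove most of that certainty at little cost

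*Protocol article*

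**What the plan says.** The Randomisation section sets the scheme: "One block of 16 random assignments will be generated for each participating mental health centre. Each block will have 8 assignments for each condition". For later patients, "If a centre includes more patients, new blocks of random assignments will be generated". No variation of block size is mentioned, and the 8:8 rule is worded for each block. The list is produced "by the independent randomisation bureau of Parnassia Psychiatric Institute".

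The same section says: "The therapists will be informed about the participation of their client and about which condition the client has been allocated". Under Unblinding, only the research assistants who run the outcome assessments are kept blind.

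Entry to the trial goes through clinicians. Under Recruitment and study procedures, patients "will be informed about the study by their treating specialist". A call from a research assistant follows, then two weeks to decide, consent, screening and baseline, and only then allocation.

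The article is dated 17 March 2020. Trial status gives recruitment as August 2018 to a predicted end in July 2020.

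**The concern.** In a balanced block of known size, once one arm has received its 8 assignments, every remaining assignment in the block belongs to the other arm. The independent bureau protects the list, but it cannot stop someone from counting allocations that have already been disclosed. The trial is open to therapists, so concealment of the next assignment depends on its being unpredictable.

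If those who put patients forward could foresee an assignment, they could hold back or bring forward particular patients. The arms would then differ at entry in ways that adjustment for the baseline score removes only in part. The question is how many assignments are exposed, to whom, and how much bias could follow.

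**Working it through.** **Inputs from the protocol article.** Block of 16, 8 per arm, per centre (Randomisation). 128 participants, planned effect 0.50, alpha 0.05, power 0.80 (Sample size). The article gives no figure on predictability. Its sample size reproduces: a two-sided t-test needs 63.77, so 64 per arm, with power 0.801. It is unaffected by this point. 128/16 = 8 full blocks.

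**1. Full tally, block start known.** With m = 8 per arm, the chance that at least the last k assignments are forced is 2 × C(16−k, 8)/C(16, 8), where C(16, 8) = 12,870.

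| k | Probability |
|---|---|
| 1 | 2 × 6435/12870 = 1.000 |
| 2 | 2 × 3003/12870 = 0.467 |
| 3 | 2 × 1287/12870 = 0.200 |
| 4 | 2 × 495/12870 = 0.077 |

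Summing over k = 1 to 8 gives 2m/(m+1) = 16/9 = 1.78 per block, or 1.78/16 = 11.1%. In 53% of blocks only the 16th assignment is certain. Over 8 completed blocks, 8 × 1.78 = 14.2 of 128 participants. Unfinished blocks would lose most or all of their forced tail.

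**2. Only DBT entries seen, block boundaries known.** The expected run of TAU after the eighth DBT assignment is m/(m+1) = 8/9 = 0.89 per block. It is non-empty in half of blocks.

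**3. Incomplete tracking.** Here each allocation is seen independently with probability q, and an assignment is certain only once 8 of one arm have been seen (40,000 simulated blocks). Visibility is an assumption, so a range is shown.

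| q | Certain per block | Share of 16 |
|---|---|---|
| 1.00 | 1.78 (exact) | 11.1% |
| 0.90 | 0.76 | 4.8% |
| 0.75 | 0.17 | 1.1% |
| 0.50 | 0.007 | 0.04% |

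**4. Possible bias from certain assignments.** Assume that patients steered into forced DBT places and those steered into forced TAU places differ by 0.5 SD in prognosis, and that every forced place is exploited. Shift = share × 0.5:
- full tally: 0.111 × 0.5 = 0.056 SD, about 11% of the planned 0.50
- 90% visibility: 0.048 × 0.5 = 0.024 SD
- 75% visibility: 0.011 × 0.5 = 0.005 SD

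The shift is proportional to the assumed difference, so halving 0.5 SD halves each figure.

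**5. Best guess.** Always guessing the arm that lags behind gives m + 2^(2m−1)/C(2m, m) − 1/2 = 8 + 2.546 − 0.5 = 10.05 correct of 16, or 62.8% against 50%.

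**6. Alternatives.** The observer in the mixed schemes sees every allocation and knows the set of sizes, but not which size is in use (simulated, sequences of 128).

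| Scheme | Certain | Best guess correct |
|---|---|---|
| Fixed 4 | 33% | 71% |
| Fixed 8 | 20% | 67% |
| Fixed 16 | 11.1% | 62.8% |
| Mixed 4/6/8 | 2.0% | 68% |
| Mixed 8/12/16 | 1.6% | 64% |
| Mixed 12/16/20 | 1.2% | 62% |

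**The case against.** A reader might infer that clinicians who refer patients know the last assignments of each block and can steer referral accordingly. The documents do not support that.

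- **No tally is described.** Each therapist is told about their own client. Nothing gives anyone a centre's running count or the block boundaries. Therapists work in one condition only. The DBT team meets weekly and could pool its counts, but that is inference, and no such meeting is described for TAU.
- **Counters and referrers need not be the same people.** The treating specialist refers, and the call, decision period, consent, screening and baseline all come before allocation. Aiming a patient at a given place is hard, though a referral can still be delayed or withheld.
- **The Discussion is not evidence of steering.** It says "therapists may be more reluctant to recommend this treatment to their clients", but as a possible hindrance to recruitment, answered by information sessions. It does not concern referral in view of a foreseen assignment.
- **Publication came late.** It left roughly 4 of 24 planned months. Whether clinicians knew the size before then is not stated.
- **Sixteen is already a good size.** It is harder to predict than fixed blocks of 4 or 8.
- **The analysis adjusts for baseline value and site,** which gives partial protection.

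All of this stands, and it is why the 11% is an upper bound and the point is minor. It does not remove the mechanism. A fixed size leaves avoidable certainty at the end of each completed block, and an independent list-holder cannot prevent deduction from known allocations.

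**Conclusion.** The design weakness is real and modest. The fixed 8:8 block of 16 makes on average 1.8 assignments per block certain to someone with a full count and a known block start. It makes about 0.9 certain to someone who sees only DBT entries, and far fewer when tracking is incomplete.

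The bias that certain assignments could cause is at most about 0.06 SD. This rests on complete tracking, full exploitation of forced places, completed blocks and an assumed prognostic difference of 0.5 SD. It falls to about 0.02 SD at 90% visibility and about 0.005 SD at 75%. These figures do not count steering on mere guesses, which the remedy does not reduce either.

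The article contains no contradiction or wrong figure here, and nothing in it shows that steering happened or was likely. The change is worth making because it is nearly free.

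**What to change.** For any block still to be generated, the independent bureau should draw the block size at random from large values, for example 12, 16 and 20. Sizes and block boundaries should not be disclosed to the centres. Small mixed sizes such as 4, 6 and 8 should be avoided, because they raise the best-guess rate to 68%. Allocation after consent and baseline is already the stated order and needs no change.

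The effect is to cut certain assignments from about 11% to about 1%, even for an observer who knows the set of sizes. The best-guess rate stays at about 62-63%.

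The cost is a setting in list generation. An unfinished block could leave a slightly larger imbalance, and DBT groups would fill less regularly. Sample size and analysis are unchanged. If few or no blocks remained to be generated, the benefit shrinks accordingly.

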### Study interventions

The therapy consists of DBT skills training [46], individual cognitive behavioural therapy [47], and weekly meetings with the consultation team for all trainers and therapists for 1 h. The complete staff will be supervised once a month by a fully certified trainer and supervisor ([name]).

Two adaptations were made to the standard DBT program for this study protocol. First, the telephone consultation (if needed) was limited to the therapist’s availability, which means that not all patients could use 24-h consultation. Second, the treatment period is limited to half of the original treatment time (1 year) because of the expected reduced concentration span. The preference for repetitive instructions in people with ASD, in combination with the concentration span, led to the decision to offer the skills training twice a week [48].

Individual cognitive behavioural therapy will take place on a weekly basis. The order and topics of each session are pre-determined based on Linehan’s hierarchy [15, 16]: suicidal and self-destructive behaviour, therapy interfering behaviour, quality of life interfering behaviour, and generalisation of the skills taught in the training. Each therapy session starts with self-report diary cards [49] that describe problematic behaviours and behaviours that influence the primary goals such as alcohol and drug use, the urge to self-harm, substance abuse, dissociation, level of applied skills, etc. Two skills training groups will take place each week. The skills taught are self-regulation skills, change skills, self-acceptance and acceptance of others, mindfulness, interpersonal effectiveness, and skills to cope with crises. When a meeting is missed, the participant will be asked to catch up by watching video recordings that are made of all the trainings sessions. The therapists keep track of self-reported watching by the experimental subjects. We consider that being in the programme for 5 months is the minimum number of sessions required for an adequate amount of intervention. All therapists are either psychologists or psychiatrists and skill trainers are psychologists, registered nurses, or social workers (*n* = 28). They will have 5 days of training in DBT by a licensed DBT therapist, teacher, supervisor, and trainer (AH).

The control group will receive treatment as usual. This can be any form of treatment for suicidality in autism which is common within mental health care and is delivered in weekly sessions of 30–45 min with a psychotherapist or social worker. Therapists will only participate in one of the conditions.

